#### Step 4: Finalise a tested, costed and improved HWPM and an implementation guide and training manuals

*End line Motivation tool:* The same health facilities visited during the baseline data collection will be visited again during the end line and the sample size of 280 will be recruited. While following up individuals cannot be achieved as this might undermine validity as health workers would be concerned about confidentiality, this approach will provide and strong indication of changes in health worker motivation over the course of the intervention.

*End line Collection of routine health service outcomes data* for indicators i.e. institutional delivery, delivery by Skilled Birth Attendant, 4 ANC visits, TB case finding and treatment outcome.

*Conduct Final Analysis*: The qualitative data will be analysed throughout the study in order to inform the emergence of themes, the further sampling of participants and interview guides to be used. In this last phase the case studies will be written up and themes that emerge across the case studies will be identified, in particular the factors influencing the success, or not, of the implementation of the model and how the different contextual factors influence this. The quantitative and qualitative data will be triangulated to explore, for example any anomalies where by health facilities whose staff appear very motivated (from the Motivation tool) but have poor indicators from the routine data. The qualitative data will help illuminate and explain anomalies and bring understanding to why the intervention may work or not is certain circumstances.

*Assess basic costs of the model:* the costs of the intervention will be collated and analysed. Incremental cost effectiveness will be calculated to show the cost per change on the motivation tool.

*Ongoing policy and influencing work:* throughout the intervention the team will engage with MoHP working groups and structures on human resources and workforce performance. In particular, the team will ensure that lessons learnt from this model are fed into the Implementation plans following the HR Strategic plan and the design of NHSSP 3.

### **Sampling**

Measuring Change in Motivation: Sample Size Calculation

The piloting of the motivation tools will provide more appropriate Nepal-specific information such as between individuals standard deviation (s.d.). However, for the purposes of planning the Mbindyo et al’s scale has been used to estimate the required sample size in order to detect a psychologically/clinically significant difference before the intervention and 20 months later.^1^ Mbindyo et al found a between individuals s.d. of 11 units.^44^ The mid-point of the Mbindyo et al scale is 30.- Assuming a 10% change (i.e. 3 points) is of clinical/ psychological significance then across the three districts, a random sample of 280 health workers will be invited to complete the motivation questionnaire at baseline; a different random sample of the same size will be selected post-intervention.  Assuming around a 10% refusal rate, this should provide 250 analysable questionnaires at both assessment times.  The mid-point of the motivation scale is 30 points; assuming a standard deviation of 11 points, this sample size will provide 86% power to detect a mean change in mean motivation score from baseline to post-intervention of 10% (3 points), with an alpha level of 5%.  The detectable change in mean score, with 90% power, at each of the participating districts is: Rasuwa 16% (4.7 points); Dang 18% (5.3 points); Baitadi 25% (7.5 points).

Table 7: Sample size of health workers in three districts

| **District** | **Region/ecology** | **Required Sample**  **Size** |
| --- | --- | --- |
| Rasuwa | Central/Mountain | 51 |
| Dang | Mid western/Plain (Terai) | 100 |
| Baitadi | Far western/Hill | 129 |
|  | Total | 280 |

Sampling of Health Facilities

In order to provide a spread of the required sample size across the different health facility levels, half of the total number of each level of health facility will be sampled. The required number of sampled health facilities will be recruited to give a spread based on high, low and moderate performance. This sampling process will be done in close collaboration with the DPHOs office in each district.

From these facilities the required sample of health workers will be recruited. Recruitment will be monitored to ensure that there is the required representation of the different levels of health facilities, health worker cadre and gender balance. If any of these groups appear to be disproportionately being recruited then remedial action will be taken.

Table 8: Health facilities to be recruited in the study

|  | **Hospital** | **PHCC** | **HP** | **SHP** | **Estimation of available health workers for recruitment** | **Required Sample**  **Size** |
| --- | --- | --- | --- | --- | --- | --- |
| Rasuwa | 1 | 1 | 7 | 1 | 67 | 51 |
| Dang | 1 | 2 | 7 | 10 | 103 | 100 |
| Baitadi | 1 | 2 | 7 | 25 | 148 | 129 |
|  |  |  |  |  | 318 | 280 |

Qualitative Sampling

Health workers will be purposively sampled to provide age, gender, caste/ethnicity balance, and also an even representation of different cadres of staff. The approximate numbers are indicated in the section above, however these may change in order for data saturation to be reached on particular issues. There will also be an element of ‘theoretical sampling’^14^, whereby, if explanations – or theories – begin to emerge that highlight why the interventions may be working for some staff and not others in different contexts, then the sampling strategy for qualitative interviews will be adapted to explore these issues further with the relevant staff. This will give deeper insights into why the intervention may or may not work for different staff in different contexts.

Community members will be purposively sampled for the focus groups which are part of the context analysis. As described above, this will be based on gender, class, caste and ethnicity. There has been a policy move within Nepal to ensure the HFMCs have representatives from disadvantaged caste and ethnic groups, particularly Dalit and Janajati, and also that there is gender balance. In order to explore how far this diversity is achieved in practice and how to work with HFMC’s to improve representation of disadvantaged groups.

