| 3. To develop, refine and test a HWPM model in 3 different districts, assess processes, effectiveness and scalability | Initial intervention design workshop.  Mid point national workshop for implementing districts to share experiences and lessons learned and to inform Nepal Health Sector Development Programme 3.  In-depth interviews, focus group discussions and ethnographic observations. Iterative adaptation of the intervention package where appropriate.  Reflective workshops for HW and district officials in each district on the successes and challenges of the intervention.  Collect and review health facility data and routine HMIS data through time  Follow up health workers from baseline and repeat collection of motivation questionnaire.  Assess basic costs of the model  Ongoing policy and influencing work, through engagement with MoHP working groups and structures on human resources and workforce performance. | Framework analysis of qualitative data (reflective workshops, IDIs and observational data) to identify barriers and facilitators.  For routine data: descriptive statistics  For Motivation questionnaire: descriptive and analytical statistics | Process evaluation data collection of implementation:  Month 7 to Month 20  Endline data collection and final analysis/report writing  Month 21 to 24 |
|  |  |  |  |

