*Recruitment of community members:* If community members from the groups identified above are potentially interested in the study, the researchers will talk through the information sheet and consent process. If the potential participant is still interested in being part of the focus group, the researchers will let them know the time and the venue. At the start of the focus group the researchers will again go through the information sheet and take informed consent from the participants, including consent to record the FGD.

*Maintaining Confidentiality and Storage of Data:* All transcripts and questionnaires will be anonymised. The identity of the participants will not be known to others apart from the research team. The researcher will write the unique identifier on the consent form, once consent has been given and this unique identifier will then be used on all collected data. The consent forms will be kept in a locked drawer in HERD’s office which is locked and has a security guard. All data and analysis on HERD’s computers will be under a password protected system.

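### The endline motivation sample is described inconsistently, and with broadly stable staffing most of it would be baseline workers, so the two rounds are not the independent samples behind the 86% power

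*Protocol*

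**What the plan says.** The protocol describes the endline motivation survey in three places.

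- **Sampling (sample size calculation).** At baseline "a random sample of 280 health workers will be invited to complete the motivation questionnaire at baseline"; afterwards "a different random sample of the same size will be selected post-intervention". About 10% refusal is assumed, leaving 250 analysable questionnaires per round. With a standard deviation of 11, this is said to give 86% power for a 3-point change at a 5% alpha.
- **Step 4 (End line Motivation tool).** "The same health facilities visited during the baseline data collection will be visited again during the end line", and 280 are recruited. On individuals: "While following up individuals cannot be achieved as this might undermine validity as health workers would be concerned about confidentiality".
- **Procedures, Table 4, objective 3.** "Follow up health workers from baseline and repeat collection of motivation questionnaire".

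Table 8 sets the workers estimated to be available in the sampled facilities against the required sample. The tightest row is "Dang | 1 | 2 | 7 | 10 | 103 | 100", that is, 103 available and 100 required. The totals are 318 and 280. The Analysis section compares mean scores before and after by ANOVA, followed by regression, and mentions neither overlap nor pairing. The Background lists high staff turnover as a known problem but gives no rate.

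**The concern.** Table 4 describes a cohort, Step 4 an unlinked repeat survey of the same facilities, and Sampling a new sample. When staff come and go, these do not measure quite the same thing: a cohort gives change in workers who stay, while a repeat survey gives change in the mean of whoever is in post. Field staff cannot both follow baseline workers and not follow them.

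The second problem is the size of the pool. Nearly all available workers are invited at baseline, so a second sample of 280 from the same facilities must draw largely on the same people. Scores from one person 20 months apart are likely to be correlated, and a two-independent-samples calculation ignores this. At stake are the standard error, confidence interval and p-value for what the Analysis section treats as the main outcome. The estimated mean change itself is not biased by the overlap.

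**Working it through.** **1. Reproducing the stated power.** Inputs from Sampling: n = 250 per round, SD = 11, difference = 3, alpha 5% (sidedness not stated; two-sided used).

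SE = 11 × √(2/250) = 0.984. Power = Φ(3/0.984 − 1.96) = Φ(1.089) = 86.2%. The plan's 86% therefore reproduces as a comparison of two independent samples of 250.

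**2. How many new workers are left.** Inputs from Table 8: available (A) and required (R). Uninvited after baseline = A − R. Minimum repeats among endline invitees, with no turnover = 2R − A.

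| District | A | R | A − R | 2R − A | Share of R |
|---|---|---|---|---|---|
| Rasuwa | 67 | 51 | 16 | 35 | 69% |
| Dang | 103 | 100 | 3 | 97 | 97% |
| Baitadi | 148 | 129 | 19 | 110 | 85% |
| Total | 318 | 280 | 38 | 242 | 86% |

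- Counting respondents rather than invitees, the floor is 2 × 250 − 318 = 182 of 250 (73%).
- If the second sample is simply redrawn with overlap allowed, the expected number of repeat invitees is the sum of R²/A: 38.8 + 97.1 + 112.4 = 248.3 of 280 (89%).
- For no invitee to repeat, at least 242 of 318 posts (76%) would need a new occupant, and in Dang 97 of 103 (94%).
- Two separate samples need 560 people. Table 5 counts 105 + 205 + 263 = 573 staff in the three districts, so they would fit only by using essentially every facility. That conflicts with sampling half of the facilities at each level and with revisiting the same ones.

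**3. Effect of worker overlap alone on the standard error.** Let f be the fraction of endline respondents who also responded at baseline, and r the within-worker correlation.

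True variance of the difference = (2 × SD²/n) × (1 − f × r). The independent-samples SE is too large by the factor 1/√(1 − f × r).

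Neither turnover nor r is in the documents. Assumed ranges: turnover 0% to 50%, r 0.3 to 0.7. Without turnover, f = 280/318 = 0.88 if the same people refuse both times, or 250/318 = 0.79 if refusals are independent between rounds. Turnover multiplies f by (1 − turnover).

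| Turnover, r | Same refusers (f from 0.88) | Independent refusals (f from 0.79) |
|---|---|---|
| 50%, 0.3 | 1/√(1 − 0.132) = 1.07 | 1/√(1 − 0.118) = 1.06 |
| 30%, 0.5 | 1/√(1 − 0.308) = 1.20 | 1/√(1 − 0.275) = 1.17 |
| 0%, 0.7 | 1/√(1 − 0.616) = 1.61 | 1/√(1 − 0.550) = 1.49 |

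The SE is thus 7% to 61% too large, or 6% to 49% with independent refusals.

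**4. Effect on the test, overlap alone.** At the respondent floor f = 0.73 and r = 0.3 / 0.5 / 0.7, the unpaired test has a true type I error of about 2.7% / 1.4% / 0.5% instead of 5%. Its power for 3 points is about 89% / 91% / 94%. It is conservative, not underpowered.

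**5. What step 3 leaves out.** Table 8 has 10 + 20 + 35 = 65 facilities, and group monitoring and action planning are delivered at facility level. If scores in a facility move together between rounds, the variance of the before-after difference gains a term that the independent-samples SE also omits. That term pushes the true SE up. The documents give no figure for it.

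**The case against.** The strongest case on the other side has five parts.

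- **The contradiction may be narrower than three designs.** Step 4 and Sampling fit together if the endline sample is meant only to be newly drawn, and Table 4 is introduced as a summary of steps detailed later. This stands. It leaves one direct contradiction (Table 4 against Step 4) and one ambiguous word. It does not restore independence, because a redraw would share about 89% of invitees.
- **Turnover.** A reader might infer that a separate endline sample is impossible. The documents do not go that far: Table 8 is an estimate, and turnover is called high without a rate. Replacement of 76% of posts within the study period is implausible rather than excluded.
- **The error may be harmless.** A reader might infer that overlap leaves the study underpowered, or that the intervals are certainly too wide. Neither follows. Overlap alone makes the test conservative, and facility-level change could offset or outweigh it. Nor can the plan claim the roughly 95% to 96% power that an analysis using the dependence would have at 30% turnover and r = 0.5, since the planned unlinked ANOVA does not use it.
- **Confidentiality.** Because "The researcher will write the unique identifier on the consent form" and that identifier is then used on all data, a reader might infer that the reason for not linking is empty. It is not. Step 4 gives a deliberate reason and Ethical issues adds fear of reprisals; an existing identifier does not show that staff would accept linkage across rounds.
- **Emphasis and the SAP.** The study focuses on process evaluation, and the choice of standard error is often left to an SAP. This lowers the severity. The conflicting definitions and the pool in Table 8 are nevertheless in the protocol itself.

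**Conclusion.** The point holds in limited form. Table 4 contradicts Step 4 and Sampling on whether baseline workers are followed. With broadly stable staffing, the sampled facilities cannot supply a second sample made up of other people: at least 86% of endline invitees, or 73% of respondents, would be repeats. The 86% power is correct arithmetic for independent samples, but the planned data will not have that structure, and the ANOVA's standard error, confidence interval and p-value will not match them.

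The overlap counts rest on Table 8's staffing estimates and low turnover. The 6% to 61% range rests on assumed turnover and within-worker correlation and covers worker overlap only. The net direction of the error, once facility-level change is included, is not known. Severity: should-fix.

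**What to change.** - State one design in Table 4, Step 4 and Sampling. The simplest that agrees with most of the present text is an unlinked repeat survey of the same facilities. Remove the follow-up entry from Table 4 and the word calling for a different sample from Sampling.
- State the expected overlap from Table 8 and the turnover assumed.
- Describe the 86% as an independent-samples approximation.
- Use facility-clustered (robust) standard errors for the before-after term. Workers sit within revisited facilities, so clustering on the 65 facilities covers both repeated workers and shared facility change without linking anyone. Staff who move between sampled facilities are a minor caveat.
- Linking by a code is optional. It would allow the repeated measurement to be used, but must be weighed against the confidentiality concern in Step 4 and Ethical issues, and settled before baseline consent.

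The cost is protocol wording and a standard model option in the software already planned. Only the optional linkage affects participants, through the information sheet and possibly their willingness to answer.

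### The detectable changes printed for Rasuwa and Baitadi are interchanged: Rasuwa has about 53% power, not 90%, for the 4.7 points credited to it

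*Protocol*

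**What the plan says.** The sample size paragraph in the Protocol's Sampling section (Measuring Change in Motivation) sets out a before/after comparison of mean motivation score between two separate samples: "a different random sample of the same size will be selected post-intervention". The target is a 3-point change: "Assuming a 10% change (i.e. 3 points) is of clinical/ psychological significance". The percentages are taken on a base of 30: "The mid-point of the motivation scale is 30 points". The pooled statement is "assuming a standard deviation of 11 points, this sample size will provide 86% power" "with an alpha level of 5" per cent, on 250 analysable questionnaires per round after about 10% refusal from 280.

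The next sentence gives the detectable change at 90% power in each district: "Rasuwa 16% (4.7 points); Dang 18% (5.3 points); Baitadi 25% (7.5 points").

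Table 7 follows with the district samples, including the rows "Rasuwa | Central/Mountain | 51" and "Baitadi | Far western/Hill | 129"; Dang has 100. Table 8 repeats 51, 100 and 129.

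**The concern.** The paragraph uses a single standard deviation, alpha and power for all three districts, so the detectable change depends only on the sample size and must fall as the sample rises. The printed order runs the other way: 4.7 points for 51 workers, 5.3 for 100 and 7.5 for 129. That is impossible before any formula is applied.

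The sample sizes are not the misprint. Tables 7 and 8 agree, and the allocation tracks the staff totals in Table 5 (105, 205 and 263): 51/105, 100/205 and 129/263 are each about 49%.

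The study sets out to learn how the model performs in mountain, hill and plains settings, and this sentence is the protocol's only statement of what each district's quantitative sample can show. Rasuwa is the only mountain district. A reader relying on the sentence would believe it has the sharpest comparison, and could take an unremarkable result there as evidence against a 4.7-point change that the sample had little better than even odds of detecting. Baitadi, the best-powered district, would be described as the weakest.

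**Working it through.** **Inputs** (Protocol, Sampling and Table 7): SD 11; alpha 5%; two independent samples of equal size; 10% refusal; 90% power for the district figures; percentage base 30 points; invited per round 51, 100 and 129. Sidedness is not stated; two-sided is used because it reproduces the pooled power.

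**Step 1: reproduce the pooled figure.**
- Standard error of the difference = 11 × √(2/250) = 0.984.
- Power = Φ(3/0.984 − 1.960) = Φ(1.09) = 86.2%.
- The protocol prints 86%, so the method is confirmed. A one-sided test would give 92%, which does not match.

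**Step 2: detectable change by district.** Formula: (1.960 + 1.282) × 11 × √(2/n), with n equal to 0.9 times the Table 7 figure.

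| District | Invited | Analysable n | Computed change | As % of 30 | Printed |
|---|---|---|---|---|---|
| Rasuwa | 51 | 45.9 | 7.44 (7.52 at n = 45) | 25% | 4.7 (16%) |
| Dang | 100 | 90 | 5.32 | 18% | 5.3 (18%) |
| Baitadi | 129 | 116.1 | 4.68 | 16% | 7.5 (25%) |

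All three printed values are recovered, with Rasuwa and Baitadi exchanged.

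**Step 3: work backwards.** The n per round needed for 90% power is 2 × [(1.960 + 1.282) × 11 / change]², rounded up.
- 4.7 points: 116
- 5.3 points: 91
- 7.5 points: 46

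These match the analysable samples of Baitadi, Dang and Rasuwa respectively.

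**Step 4: power for the values as printed.**
- Rasuwa, 4.7 points: SE = 11 × √(2/45.9) = 2.296; Φ(4.7/2.296 − 1.960) = Φ(0.087) = 53%.
- Dang, 5.3 points: 90%.
- Baitadi, 7.5 points: SE = 11 × √(2/116.1) = 1.444; Φ(7.5/1.444 − 1.960) = Φ(3.23) = 99.9%.

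**Step 5: try other readings.**
- No refusals: Rasuwa 7.06, Baitadi 4.44; Rasuwa's power for 4.7 points is 58%.
- Refusal as 250/280, rounding down, or a t-based calculation: Rasuwa 7.5 to 7.6, Baitadi 4.7; Rasuwa's power is 52% to 53%.
- One-sided 5%: Rasuwa 6.7, Baitadi 4.2; Rasuwa's power is about 65%.
- 80% power instead of 90%: Rasuwa 6.4, Baitadi 4.0.
- Finite-population correction using the Table 5 totals: Rasuwa 5.6, Dang 4.0, Baitadi 3.5.

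None gives 4.7 for Rasuwa or 7.5 for Baitadi, and none reverses the order.

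**The case against.** The arithmetic is hard to dispute; the fair challenge concerns how much it matters.

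- **The design does not rest on these figures.** The sample of 280 comes from the pooled calculation, which is correct, and the allocation follows staff numbers. This stands: no recruitment target changes.
- **No separate district test is spelled out.** The Analysis section describes ANOVA of before and after scores and a regression on worker and workplace characteristics, with 95% confidence intervals. Those intervals would reflect the actual sample, and the process evaluation and case studies carry much of the question of how the model works in each setting. This also stands. It confines the harm to planning and to how district results are read.
- **No district is powered for 3 points anyway.** By the same formula, power for 3 points is about 26% in Rasuwa, 45% in Dang and 55% in Baitadi. That is true, but it makes a correct statement of what each district can detect more useful, not less.
- **The 53% is conditional.** It assumes a two-sided test, 10% refusal and simple random sampling, whereas workers are recruited within sampled facilities. This stands as a caveat. Clustering would not be expected to favour Rasuwa: Table 8 lists 10 facilities there and 35 in Baitadi, so 51/10 = 5.1 and 129/35 = 3.7 workers per facility.

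These points limit the reach of the error. None makes the printed sentence true.

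**Conclusion.** The sentence is wrong as written. The Rasuwa and Baitadi figures are transposed, and Dang's is correct. On the protocol's own assumptions (SD 11, independent rounds, two-sided 5%, 10% refusal, no allowance for clustering), the 90%-power detectable change is about 7.5 points in Rasuwa and 4.7 in Baitadi. Rasuwa's precision is overstated by 7.5 − 4.7 = 2.8 points, and its power for the printed 4.7 points is about 53% instead of 90%; the other readings tried put it between 52% and 65%. Baitadi's precision is understated by the same 2.8 points. That the order is impossible follows from the common SD, alpha and power alone; it does not depend on sidedness or the refusal rate. The pooled power statement is unaffected.

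**What to change.** In the Sampling section, exchange the two values so that the sentence gives: Rasuwa 25% (7.5 points); Dang 18% (5.3 points); Baitadi 16% (4.7 points). It would help to add that these are on the same basis as the pooled figure: two-sided 5% test, SD 11, 10% refusal, no allowance for clustering within facilities.

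The cost is one sentence. Tables 7 and 8, the pooled sample size, recruitment and budget stay as they are. The stated figure for Rasuwa becomes less favourable, and any material that repeats the district figures should be corrected to match.

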| **2. Community Assessment** | Community assessment of facilities and action planning are an integral part of the group monitoring exercise. During the peer monitoring visit, officers from DPHO and members of the HFMCs conduct rapid participatory appraisal PRA exercises with communities to identify the positive aspects of the health facilities and the areas they wish to improve. This community feedback is then presented along with the group monitoring feedback to the facilities’ action planning workshop.  During the workshop the facility staff and the HFMCs are facilitated by the group monitoring team to identify specific actions they can undertake to improve their health facility. The emphasis is on the actions being achievable by the clinic staff themselves, rather than requiring external financial or other assistance. | To improve accountability and ensure staff feel motivated to provide a service that meets the needs of their communities.  If positive feedback is received this can motivate staff.  If negative feedback is received this can encourage staff to make changes so as not to appear to be letting their communities down. |
| **3. Supportive supervision and feedback** | Health workers are appraised regularly (at least annually) by their colleagues. Each HW is appraised by four other staff: 1 from the DPHO, 1 colleague of the same professional level from outside the health facility and from the same level HF and 2 colleagues from within the health facility (normally one will be the in-charge). Individual workplans in line with the targets for the health facility will be set. While this intervention goes against the hierarchical relationships found within Nepal’s health workforce, it has been seen to work within Doti district particularly with a strong lead from the DPHO, who clearly endorsed the approach. | To reduce bias which may occur when appraisals are done by only one manager, normally the in-charge.  To encourage professional development through peer support  To link performance review with action plans to improve performance in line with facility targets. |

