#### Step 2: Developing and Introducing the Intervention

Based on the lessons learnt from the Doti work, the context analysis and from HRM evidence, the intervention will be finalised. Section 2.3 describes the basis for the proposed intervention. An initial intervention design workshop will be held with the full research team and key stakeholders from each district.

Exactly how the elements of the HR model are operationalised in each district will be developed in close collaboration with the District Health Office (DHO). In order to prepare the health facilities for this new way of working workshops to introduce the new approach to monitoring and supervision and the development of job aids will draw on the techniques used in Appreciative Inquiry. These approaches help health workers to appreciate the benefit that they can provide to their communities and identify the assets they have as individuals and within the health system to provide quality care. A national workshop for the three implementing districts will be held six months into implementation to share experiences and lessons learned and to inform Nepal Health Sector Development Programme 3. Both the initial workshop and this mid-term workshop will provide valuable data for the process evaluation. As such, a detailed record of both workshops will be kept and analysed as part of the qualitative analysis. The mid-term workshop in particular, may highlight process issues that can be followed up through individual interviews and observation by the research team.

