# Ethical issues

The study team will work closely with District Authorities and community leaders to ensure that all stakeholders are well informed of the study and its purpose. The study will be reviewed by Ethical Review Committee of WHO, it will also seek ethical approval from the Liverpool School of Tropical Medicine and from Nepal Health Research Council (NHRC).

*Potential Issues:* health workers may feel unable to refuse participation or able to speak freely for fear of reprisals from senior managers. To address these issues during recruitment research staff will explain clearly that all data provided whether by questionnaire (motivation tool) or during qualitative interviews will remain anonymous. We will be careful in the characterisations used to locate quotations, for example not naming Districts directly (referring to Hill district or Terai District, rather than by name) in order to maintain confidentiality during reporting and dissemination.

All participants, whether they are health workers, district officials or community members will be given sufficient information about the study and be provided with opportunity to ask any questions and think over participation on their own before giving consent.

*Recruitment for Interviews with staff and HFMC members:* The research team will visit each of the randomly selected health facilities (as above) and present to all staff and to HFMC members: the study, its purpose and inclusion criteria for both the questionnaire and the qualitative elements. They will then leave information sheets and consent for all staff to read, allowing at least 24 hrs to consider their participation or not. They will make a time with the health facility to return to conduct the motivation questionnaire and qualitative interviews. At these start of these interviews the participants will be encouraged to ask any questions about the study. If they are still willing to participate, they will then fill in their consent form.

The researcher will be well trained to explain the study and the HWs right not to be involved should they wish so or leave the interview at any point of time. Qualitative interviews will be conducted at a private location away from the health facility to ensure confidentiality.

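### The survey facilities are called randomly selected, but the sampling rule names no random draw and involves the district office that helps deliver the intervention

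*Protocol*

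**What the plan says.** Several parts of the Protocol bear on how the motivation survey is sampled.

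- **Sampling, sample size calculation.** At baseline, "a random sample of 280 health workers will be invited to complete the motivation questionnaire at baseline"; for endline, "a different random sample of the same size will be selected post-intervention".
- **Sampling, health facilities.** "half of the total number of each level of health facility will be sampled". Then: "The required number of sampled health facilities will be recruited to give a spread based on high, low and moderate performance". Then: "This sampling process will be done in close collaboration with the DPHOs office in each district". Workers are recruited from these facilities, with checks on facility level, cadre and gender. No draw is described at either step.
- **Ethical issues, recruitment of staff.** "The research team will visit each of the randomly selected health facilities (as above"). The same paragraph has the team return to these facilities for the motivation questionnaire, so the wording covers the quantitative sample.
- **Role of the district office.** In Table 3 (Study goal and objectives), "officers from DPHO and members of the HFMCs conduct rapid participatory appraisal PRA exercises with communities", and one of each worker's four appraisers comes from that office. In Step 2, the way the model is put into practice in each district "will be developed in close collaboration with the District Health Office (DHO").
- **Use of the sample.** Step 4 returns to the same facilities at endline. The Analysis section compares mean scores by ANOVA with 95% confidence intervals and p values.

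**The concern.** The ethics text points back to a random selection that the Sampling section does not contain. What that section does contain is a performance criterion, applied together with an office that has a part in designing and delivering the model under test.

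Two things are at stake. First, confidence intervals and p values that are meant to describe health workers in the three districts need a known selection mechanism, and none is stated. Second, without a draw nothing prevents the implementer from influencing, even unintentionally, where the change is measured. Selection precedes baseline, so later analysis cannot restore a missing draw.

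**Working it through.** **1. The plan's own figure.** Inputs from Sampling: 250 analysable questionnaires per time point, SD 11, change 3 points, alpha 5% (two-sided reproduces the figure).

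- Allowance for refusal: 280 × 0.9 = 252, consistent with about 250.
- SE of the change = 11 × √(2/250) = 0.984.
- Power = Φ(3/0.984 − 1.96) = Φ(1.089) = 86.2%, against 86% stated.

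The arithmetic is sound. The formula treats the two surveys as independent random samples of workers.

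**2. How far choosing facilities fixes the sample.** Counts are facilities taken (Table 8) out of facilities present (Table 5). Available workers and required sample are from Table 8.

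| District | Hospital | PHCC | HP | SHP | Facilities | Workers available | Required |
|---|---|---|---|---|---|---|---|
| Rasuwa | 1 of 1 | 1 of 1 | 7 of 14 | 1 of 2 | 10 of 18 | 67 | 51 |
| Dang | 1 of 2 | 2 of 3 | 7 of 15 | 10 of 21 | 20 of 41 | 103 | 100 |
| Baitadi | 1 of 1 | 2 of 2 | 7 of 15 | 25 of 50 | 35 of 68 | 148 | 129 |
| Total | | | 21 of 44 | 36 of 73 | 65 of 127 | 318 | 280 |

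- Share of available workers surveyed: 280/318 = 88%. In Dang it is 100/103 = 97%.
- HPs and SHPs are 21 + 36 = 57 of the 65 facilities, taken from 44 + 73 = 117 (49%).
- At Table 5 staffing they hold 21×5 + 36×3 = 213 of the 318 workers (67%).

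A random draw of workers inside the chosen facilities would therefore add little. The facility step decides who is in the survey, and it leaves most room for choice among HPs and SHPs.

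**3. The passages side by side.** Ethical issues asserts randomness and refers back. The only facility rule for this survey that it can refer to is the one in Sampling, which gives a fraction, a criterion and a collaborating office, but no draw. Step 3 also uses the district health officer's advice, but that concerns the case-study facilities and is a separate process.

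**4. What could bias the change.** A stable difference between chosen and unchosen facilities is present at both surveys and largely cancels. What remains is a net shift *b* from differential response or regression to the mean. The documents give no value for *b*, so the following values are assumptions. If the true district-wide change were zero, the chance of a significant result would be Φ(−1.96 + b/0.984) + Φ(−1.96 − b/0.984):

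| Assumed shift (points) | Chance of a significant result |
|---|---|
| 0 | 5% |
| 0.5 | 8% |
| 1.0 | 17% |
| 1.5 | 33% |
| 2.0 | 53% |

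As one way to reach 0.5 points, suppose some facilities improve 2 points more than the rest and form 75% rather than 50% of the sample: (0.75 − 0.50) × 2 = 0.5. The formula is symmetric in the sign of *b*. A negative shift would hide a real improvement rather than create a false one.

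**The case against.** The strongest reply is that the two sections can be read together. The Sampling section does not call this facility sample purposive, although the Protocol uses that term for the districts, interviews and focus groups. Random selection within level and performance groups would fit both texts. Close collaboration need not mean that the office chooses, since it may only supply lists and performance data. Requiring low performers also limits any favouring of good facilities. This stands in part: the inference is unsupported as written, not proven impossible.

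Three stronger readings are tempting, and the documents support none of them.

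- **That selection inflates the before-after change.** The same facilities are revisited, so stable differences largely cancel. Any remaining bias needs a differential response or regression to the mean, for which the Protocol gives no size or direction. Recruiting both high and low performers would also produce regression in opposite directions.
- **That the 86% power is wrong.** It reproduces, and nothing here yields a corrected figure.
- **That the district office controls selection or would favour cooperative sites.** The text shows involvement and a stake in the model, no more.

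It is also fair to say that the three districts were chosen purposively (Study sites), so a facility draw could support inference to those districts but not to Nepal. That limits what the fix achieves and does not answer the point within the districts.

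**Conclusion.** The point holds as a gap between what is claimed and what is specified. The Protocol calls the sample random in two places and describes no draw in the section that should contain it. An office that helps design and deliver the intervention takes part in the selection. Random-sample inference to the three districts is unsupported as written.

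The reach is wide, because the 65 chosen facilities nearly determine the survey: 280 of about 318 available workers, on the Protocol's approximate staffing. The effect on the estimated change is unknown in size and direction, and the figures in step 4 of the working show sensitivity only. This should be settled before facilities are selected.

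**What to change.** State in Sampling that the research team draws the facilities at random from a full list supplied by the district office, which does not choose among them. The numbers in Table 8 stay as they are.

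- **Draw stratified by performance group:** HPs in all three districts and SHPs in Dang and Baitadi. Three groups are workable here: 14 or 15 HPs per district give groups of 4 or 5, Dang's 21 SHPs give groups of 7, and Baitadi's 50 give groups of 16 or 17. This covers 21 + 10 + 25 = 56 of the 65 facilities. Define the groups before the draw.
- **Simple random draw:** Rasuwa SHP (1 of 2), Dang hospital (1 of 2) and Dang PHCC (2 of 3), where performance groups cannot be formed or would leave nothing to draw. This covers 4 facilities.
- **All taken:** hospital and PHCC in Rasuwa and Baitadi, as Table 8 already has it. This covers 5 facilities.

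Reword Ethical issues to match. If the facilities have already been selected without a draw, remove the word random from both sections and limit the inference to the sampled facilities.

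The cost is one documented draw, an advance definition of the performance groups and a few sentences. The intended spread of performance is kept.
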